### Statistical analysis

The findings will be reported according to the Consolidated Standards of Reporting Trials guidelines for randomised controlled trial^39^ (figure 1). This will include the flow of research participants through each stage of the trial, including the number eligible, randomly assigned, receiving the intended treatment, completing the study protocol and analysed for the primary outcome. The primary analyses will be on intent-to-treat basis consisting of all participants included according to the arms in which they are randomised and secondary analyses will be based on per-protocol population.

For the analysis of the primary outcome (caregiver–child interaction across two-arms at 12 months postpartum), a linear regression model will be employed with treatment as the sole predictor. In addition, adjusted linear model analysis will be performed with the prespecified covariates (gender of infant, mother’s education and severity of mothers’ psychosocial distress measured using SRQ) measured at baseline being added into the above linear model. The crude and adjusted mean differences in the primary outcome together with its 95% CIs at 12 months will be derived from the linear models. In addition, subgroup analysis of primary endpoint will be performed on the above prespecified covariates.

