Analysis of secondary continuous outcomes with single follow-up measurement will be done in a similar fashion as the primary endpoint analysis. Analysis of secondary continuous outcomes with repeated follow-up measurement will be performed using a linear mixed model with treatment visit, interaction between treatment and visit as fixed effects, the baseline value of the outcome as covariate, if it is available and subject as random effects. The analysis of binary outcomes will also use a generalised linear/mixed model depending on whether there will be a repeated measurement. ORs with their 95% CIs will be derived from the generalised linear/mixed model analysis. Missing primary outcome and secondary outcomes with a single measurement will not be imputed; whereas, missing secondary outcomes with repeated measurements will be imputed in sensitivity analysis using the last observation carried forward strategy. Missing baseline covariates will be imputed using simple imputation methods in the covariate adjusted analysis based on the covariate distributions in the sample. For a continuous variable, missing values will be imputed from random values from a normal distribution with mean and SD calculated from the available sample. For a categorical variable, missing values will be imputed from random values from a uniform distribution with probabilities *P*_1_, *P*_2_, … and *P*_k_ from the sample. Seed for the imputation will be set as the date of data analysis. The study is powered to make a single comparison in the primary outcome at 12 months only. All analyses will be described in detail in the statistical analysis plan. SAS V.9.4 and SPSS V.21 will be employed for the statistical analyses.

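### Missing baseline covariates are filled by what reads as one random draw seeded with the analysis date, so the adjusted estimate can change with the run date

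*Protocol article*

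**What the plan says.** All of this stands in the protocol article, Statistical analysis.

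- The first-named model for the primary outcome is crude: "a linear regression model will be employed with treatment as the sole predictor".
- An adjusted model is added to it: "adjusted linear model analysis will be performed with the prespecified covariates (gender of infant, mother’s education and severity of mothers’ psychosocial distress measured using SRQ". Both mean differences are to be reported with 95% CIs. Continuous secondary outcomes with one follow-up measurement are handled in the same way.
- On missing covariates: "Missing baseline covariates will be imputed using simple imputation methods in the covariate adjusted analysis based on the covariate distributions in the sample".
- When the covariate is continuous, "missing values will be imputed from random values from a normal distribution with mean and SD calculated from the available sample". When it is categorical, "missing values will be imputed from random values from a uniform distribution with probabilities" taken from the sample proportions.
- On the seed: "Seed for the imputation will be set as the date of data analysis".
- On outcomes: "Missing primary outcome and secondary outcomes with a single measurement will not be imputed".

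No repetition or pooling of imputations is described. The section leaves further detail to the statistical analysis plan, but the draw and its seed are already decided here.

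**The concern.** A seed is useful when it is settled before anyone sees a result. This one is unknown until the programme runs, and it changes if the programme is run again on another day, for example after a data correction. Two runs on identical data could then report different adjusted differences, intervals and p-values, and the plan does not say which one counts. If the adjusted result were borderline, a reader could not tell a routine re-run from a choice among seeds.

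The randomness also gains nothing. The values are drawn from the marginal distribution of each covariate, so they carry no information about the woman concerned. One such draw adds noise to the covariate and slightly weakens the adjustment.

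At stake are the adjusted primary result and the adjusted results for single-measurement secondary outcomes.

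**Working it through.** **The plan's own figure.** The Sample size calculations section gives d = 0.4, two-sided alpha 0.05, 80% power and 20% attrition. The two-sample t-test needs 99.08, so 100 per arm. 100 / (1 − 0.20) = 125 per arm, or 250 in total, which matches. The normal approximation gives 99 per arm, then 124, or 248 in total. The dyads expected in the analysis are 250 × 0.80 = 200.

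**Inputs from the protocol.** OMCI SD = (8.3 + 8.2) / 2 = 8.25. The planned difference is 0.4 × 8.25 = 3.3 points. Allocation is 1:1. The three covariates are infant gender, mother's education and baseline Self-Reporting Questionnaire (SRQ) score.

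**Assumptions not in the protocol.**
- Each covariate is missing completely at random in 1%, 5%, 10% or 20% of dyads.
- The covariates together explain R² = 0.10 or 0.30 of OMCI variance, split 50% education, 40% SRQ and 10% gender.
- Education and SRQ are treated as continuous.

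**Method.** 300 data sets of 200 dyads were simulated. On each, with the data held fixed, the protocol's draw was repeated under 60 seeds and the adjusted model refitted. The same data sets were also analysed with each missing value set to the overall covariate mean.

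**Check on scale.** With complete covariates the SE is about 8.25 × √(1 − R²) × √(2/100). This gives 1.107 at R² = 0.10 and 0.976 at R² = 0.30, close to the simulated 1.115 and 0.980 at 1% missing.

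| R² | Missing per covariate | Seed-to-seed SD (points) | SE, random draw | Seed SD / SE | SE, mean fill |
|---|---|---|---|---|---|
| 0.10 | 1% | 0.039 | 1.115 | 4% | 1.114 |
| 0.10 | 5% | 0.087 | 1.115 | 8% | 1.112 |
| 0.10 | 10% | 0.118 | 1.125 | 11% | 1.120 |
| 0.10 | 20% | 0.154 | 1.137 | 14% | 1.128 |
| 0.30 | 1% | 0.063 | 0.980 | 7% | 0.978 |
| 0.30 | 5% | 0.139 | 1.002 | 14% | 0.993 |
| 0.30 | 10% | 0.189 | 1.022 | 19% | 1.003 |
| 0.30 | 20% | 0.240 | 1.059 | 23% | 1.027 |

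**Reading the table.**
- A typical seed shift is 0.04 to 0.24 points, or 0.04/3.3 = 1% to 0.24/3.3 = 7% of the planned difference.
- The SE is larger than under mean fill by 0.05% to 3.1%.
- Under mean fill the seed-to-seed SD is zero.
- In 3% to 22% of data sets, p < 0.05 was met under some of the 60 seeds and not under others. With 300 data sets, the Monte Carlo SE of the upper figure is √(0.22 × 0.78 / 300) = 2.4 percentage points. This share counts any disagreement among 60 seeds, so it overstates the chance that two given runs disagree.
- With no missing covariates, every seed gives the same answer.

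**The case against.** The strongest reply is that there may be almost nothing to impute in the adjusted OMCI model.

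- SRQ is an entry criterion, and Table 2 lists it at both screening and baseline.
- A dyad with an OMCI score has an infant who was observed, so its sex can be recorded, and missing OMCI scores are not imputed.
- Education is one baseline item, and Data management describes daily data checks.

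This stands, and it is why the point is minor. The 1–20% range is illustrative. Nor can any seed touch the crude model, and the trial is powered for a single comparison of the primary outcome.

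Several stronger readings are tempting, but the protocol does not support them:

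- **That the result could not be reproduced.** A recorded date used again as the seed reproduces the draw. The fault is that the seed is not fixed beforehand.
- **That the estimate is biased.** The draws ignore arm and outcome, so they add noise only.
- **That the categorical rule is undefined.** The wording is loose, but it can be read as an ordinary draw with the sample proportions.
- **That SRQ would often be filled with values below the entry score of 9.** An unbounded normal draw could do this, but an SRQ score should exist for every woman who entered.
- **That mothers who lost a pregnancy or infant would be given a random infant sex.** The protocol lists gender among covariates "gender of infant, mother’s education and severity of mothers’ psychosocial distress measured using SRQ) measured at baseline", although baseline is in the third trimester, so its source needs stating. But it does not clearly put infant sex into models for maternal outcomes, so the scenario is speculative.
- **That the whole spread over many seeds is the likely error.** The range over 60 seeds averaged 0.18 to 1.12 points, but that is the gap between extremes. The seed-to-seed SD is the fair measure.

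A single deterministic fill does not carry imputation uncertainty either. Its advantage is that it gives one answer and needs no seed.

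**Conclusion.** The point holds as a minor one. The protocol commits to a random fill whose seed is the analysis date, so the adjusted estimate and p-value can depend on when the programme is run. That the fill is a single draw is the natural reading of the text, which does not use the word single.

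Under the assumed missingness and R², the seed contributes an SD of about 4–23% of the standard error of the adjusted OMCI difference. The true figure is probably near or below the lower end, because covariate missingness is likely to be low, and it is nil if nothing is missing. The crude primary comparison stands as planned.

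**What to change.** Replace the random draw with a deterministic fill, applied identically in both arms and without reference to arm or outcome:

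- Continuous baseline covariate: the overall sample mean.
- Categorical baseline covariate: a missing category or the mode, with the choice stated.
- SRQ: the screening score if the baseline score is missing, before any fill.
- Infant sex: taken from the birth record or first infant record, and described that way instead of as a baseline measurement.

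If random draws are kept, write a fixed numeric seed into the plan now and use multiple imputation with pooling.

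The cost is one or two sentences in the statistical analysis plan before the outcome data are analysed. No data collection, participants or sample size are affected.

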### Potential mediators

We will explore pathways through which the intervention may influence primary outcome (ie, mother–child interaction). There is strong empirical evidence that the quality of the mother–child interactions, such as her sensitivity and responsiveness, is associated with both maternal depression and child development.^40–43^ There is also some evidence that perinatal depression interventions, especially ones that include a parenting component, can improve maternal distress; maternal responsiveness, resulting in improved developmental outcomes.^44^ We will assess maternal responsiveness with the maternal items of OMCI that measure maternal responsive behaviours during mother–child interaction. The OMCI has been used to evaluate the impact of maternal interventions on maternal responsiveness.^45^ Maternal distress will be assessed using SRQ. The tool has been used extensively in the study settings previously to measure maternal distress.^46^

*Social support*: low social support is a consistent predictor of mental ill health among mothers.^47 48^ Social support can be theorised to be either a mediator or effect modifier; since building social support is a key feature of the integrated intervention, we hypothesise that increased social support will mediate the relationship between the intervention and child outcomes. *Maternal empowerment*: maternal empowerment will be assessed using two items previously used in the same population.^38^
*Breastfeeding and other health-related variables*: perinatal depression interventions similar to this integrated intervention have resulted in higher rates of exclusive breastfeeding at 6 months and increased likelihood of completion of scheduled immunisations.^6^ These health-related behaviours may contribute to the positive effect of intervention on improving maternal well-being and infant development, we will assess the impact of behaviours related to feeding (breastfeeding, introduction of solid food) and immunisations on mother–child interaction.

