#### Primary outcome

Caregivers–child interaction: maternal responsive caregiving behaviours will be assessed at 12 months’ postpartum across two-arms (primary endpoint) using the OMCI tool.^22^ OMCI tool is based on responsive parenting framework proposed by Landry and colleagues.^23^ The tool comprises of 19 items related to maternal and child behaviours. Maternal behaviours include maternal affect, maternal touch, maternal verbalisation, sensitivity and contingent responses, scaffolding, language stimulation and focus; whereas, child outcomes include, child affect, child focus, child’s communication efforts and mutual enjoyment. The scoring is done by recording the frequency of the occurrence of each of the above-mentioned behaviours during the mother–child interaction. The sum is calculated by adding the scores of mother and child domains; where higher score indicates more responsive interactions. The tool has been designed to live rate mother–child interaction of 2 years old toddlers in low resource settings of rural Pakistan. It has been extensively used in similar population in Pakistan and found to be sensitive to detect change in mother–child interaction as a result of receiving responsive caregivers intervention at 12 and 24 months postpartum.^22^ In the present study, the research assistants will observe a live 5 min mother–infant interaction while mother and infant will play together with a picture book.

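### Maternal responsiveness is to be tested as a mediator of the OMCI total using items that are part of that total, so the mediator–outcome path is positive by construction

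*Protocol article*

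**What the plan says.** Under Potential mediators, the protocol article states its aim as exploring "pathways through which the intervention may influence primary outcome (ie, mother–child interaction". For maternal responsiveness, one of the candidate mediators, it fixes the instrument: "We will assess maternal responsiveness with the maternal items of OMCI that measure maternal responsive behaviours during mother–child interaction".

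Under Primary outcome, the article says of the OMCI: "The tool comprises of 19 items related to maternal and child behaviours". The score is a total: "The sum is calculated by adding the scores of mother and child domains; where higher score indicates more responsive interactions". The same section introduces the endpoint in these terms: "maternal responsive caregiving behaviours will be assessed at 12 months’ postpartum across two-arms (primary endpoint) using the OMCI tool". All of it comes from one occasion: "the research assistants will observe a live 5 min mother–infant interaction while mother and infant will play together with a picture book".

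Table 2 schedules the OMCI, BSID-III and ASQ3 at 12 months only. MSPSS and empowerment are taken at baseline and 12 months, SRQ at baseline, 6 and 12 months, breastfeeding at 6 months, and immunisation at 6 and 12 months.

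**The concern.** Read together, these sections make the mediator a component of the outcome. The maternal items enter the OMCI total directly, so they predict it whether or not maternal behaviour influences the child. That is a part–whole relation and not a pathway. The two scores also come from the same few minutes of observation, so neither precedes the other.

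At stake is the meaning of an exploratory result. If the intervention improves maternal behaviour, the trial could report that maternal responsiveness mediates its effect on mother–child interaction, when the analysis has only shown again that part of the primary outcome improved.

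**Working it through.** **Inputs from the article.** Outcome Y = OMCI total = M (maternal items) + C (child items), from Primary outcome. Mediator = M, from Potential mediators. Effect size 0.4, 80% power, two-sided 0.05 and 20% attrition, from Sample size calculations.

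**The plan's own figure.** A two-sided t-test at effect size 0.4 needs 100 per arm; 100 / 0.8 = 125 per arm, 250 in total. This agrees with the article. It gives no figure for the mediation analysis. The simulation below uses 100 analysed per arm.

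**Algebra.** Let a be the treatment effect on M. Regress C on treatment and M, and call the slope on M b(C) and the direct treatment effect d(C). Because Y = M + C, and M regressed on treatment and M has slope exactly 1 and direct effect 0:

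- slope of Y on M = 1 + b(C)
- direct effect on Y = d(C)
- indirect effect = a × (1 + b(C))
- proportion mediated = a × (1 + b(C)) / total effect

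With no maternal-to-child link, b(C) = 0. The slope is 1 and the proportion mediated is a / total effect, which is the maternal share of the effect. For example, with a total effect of 0.40 and a = 0.28, it is 0.28 / 0.40 = 0.70.

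**Simulation.** 3,000 trials per row, within-arm SD of the total set to 1, b(C) = 0, total effect 0.4. Mediation is declared when the treatment–mediator and mediator–outcome paths both have p < 0.05. The maternal shares of effect and variance are assumptions, because the article does not give them.

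| Maternal share of effect | Maternal share of variance | Slope on M | Proportion mediated | Declared, OMCI total | Declared, child score only |
|---|---|---|---|---|---|
| 0% | 50% | 1.00 | 0.01 | 5% | 0.1% |
| 50% | 50%, 70% | 1.00 | 0.49–0.50 | 38–51% | 2.2–2.6% |
| 70% | 50%, 70% | 1.00 | 0.70 | 65–80% | 3.2–3.7% |
| 90% | 50%, 70% | 1.00 | 0.90–0.91 | 87–95% | 4.0–5.2% |
| 100% | 30%, 50%, 70% | 1.00 | 0.99–1.00 | 92–100% | 4.3–4.7% |

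With the OMCI total as outcome, the mediator–outcome path is significant in 100% of trials in every row. With the child score as outcome it is significant in 4–5%, the nominal rate. With no treatment effect at all, mediation of the total is declared in about 5%.

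**With a maternal–child association.** Take correlation 0.3, equal variances and a 70% maternal share of the effect. Then b(C) = 0.3, the slope is 1.30 and the proportion mediated is 0.28 × 1.3 / 0.40 = 0.91. Of this, 0.28 / 0.40 = 0.70 is overlap and 0.28 × 0.3 / 0.40 = 0.21 comes from the association. With the child score as outcome, mediation is declared in 89% of these trials, so excluding the overlap keeps the ability to pick up an association.

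**The case against.** **The mediation outcome may be developmental.** The article writes out no mediation model. The background evidence in the section runs from maternal responsiveness to child development, and the social support hypothesis names child outcomes. With BSID-III or ASQ3 as the outcome there would be no overlap. This is the strongest point, but the sentence that sets the aim names the primary outcome. The background sentence describes earlier evidence, and the child-outcomes wording belongs to social support alone. If development was intended, the text needs correcting in any case.

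**The analysis plan will give the detail.** It may well specify the model. But the article already names both the mediator's items and the outcome, and that pairing fails under any regression-based mediation model.

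**It is exploratory.** This stands. The study is powered for one comparison, and that comparison is untouched.

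**Part of the remedy is already planned.** This also stands: the section already intends to relate feeding and immunisation to mother–child interaction, and it names the SRQ.

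**Stronger readings a reader might infer.**
- That mediation will be found whatever the true mechanism. It will not: overlap fixes the mediator–outcome path only. The treatment–mediator path needs a real effect on the maternal items.
- That a definite percentage is built in, by counting the behaviours listed under Primary outcome. The article gives neither the maternal/child split of the 19 items nor their variances, so no single percentage follows.
- That one rater scores both parts. The article refers to research assistants without saying how many rate each session; only the shared session is stated.

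**Conclusion.** The point holds as a part–whole fault in one exploratory analysis. As written, the maternal-responsiveness mediator is an addend of the outcome it is meant to explain. Its slope on the OMCI total is 1 + b(C), hence 1 when maternal and child behaviour are unlinked. That slope result is algebraic and needs no assumption about the item split.

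The size of the artefact equals the maternal share of the treatment effect, which is not known here: the assumed range of 50–100% gives 50–100% mediated. The declaration rates of 38–100% over that range rest further on normal scores, 100 analysed per arm and the assumed variance shares. If the intervention moves the maternal items, the indirect effect says nothing about mechanism; if it does not, mediation is declared about 5% of the time.

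**What to change.** 1. State that the maternal OMCI items will not be analysed as a mediator of the OMCI total.
2. Pair them only with outcomes that exclude them: the child-domain OMCI score, BSID-III or ASQ3. State which of the 19 items count as maternal and which as child.
3. For the OMCI total, use the 6-month values of mediators already planned: SRQ, breastfeeding and immunisation.
4. Report every pairing in which mediator and outcome are both taken at 12 months as a cross-sectional association without established temporal order. This covers the maternal OMCI items with the child-domain score, BSID-III or ASQ3, and the analyses using 12-month MSPSS and empowerment.

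The cost is wording only, since every measure is already in Table 2. The downside is that a maternal-responsiveness pathway to the OMCI total can no longer be reported.

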### Cost–effectiveness analysis

Health economic analysis will be conducted to determine the difference in costs and outcomes in the intervention as compared with the control arm. The cost of the intervention will be calculated based on the sum of materials, personnel training and delivery. We will then compare the combination of the cost of the intervention and the service cost data with mother–child interaction summary scores. If the intervention results in more favourable summary scores (improvement in mother–infant interaction) and lower total costs, it will be described as superior to no intervention option. If, in contrast, the intervention results in more favourable scores but is also more expensive, then the cost–effectiveness calculation will be based on the cost and scores of mother–infant interaction outcomes.

Primary analysis will be of total costs over the 12 months postpartum follow-up treatment period. Recognising that cost data are often skewed, the bootstrap technique will be applied. The sampling with replacement from original observed pairs of costs and effects will be employed to maintain correlation structure between costs and benefits, and bootstrapping sampling will be repeated 1000 times. For each bootstrap sample, an estimate of differential total mean costs and expected mean effectiveness will be calculated. The 95% CIs for the differential estimates will be derived from the 25th and 97.5th percentiles.^49 50^

Cost–effectiveness will be assessed by combing costs with the primary outcome measure (ie, mother–infant interaction) scores in incremental cost–effectiveness analysis. Repeat resampling from the costs and effectiveness data (bootstrapping) will be used to calculate the probability that each of the treatment is the optimal choice, subject to a range of possible maximum values (ceiling ratio) that a decision-maker might be willing to pay for a unit improvement in mother–infant interaction scores. The results of the cost–effectiveness will be reported as incremental cost–effectiveness ratios, and acceptability curves which summarise the information contained in a cost–effectiveness plane.^51^

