### Intervention

The intervention called ‘Nurturing Care’ combines common elements from evidence-based interventions for maternal psychosocial distress (eg, WHO Thinking Healthy Programme^17^), early stimulation and responsive feeding (eg, Unicef Care for Child Development Package^15^) and child care (eg, WHO Caregivers Skills Training programme^16^) for optimal development of at risk mother and children.

The intervention package aims to improve (a) mother psychological distress by promoting problem solving, developing empathic listening, improving family support, using guided discovery through pictures and behavioural activation; (b) child development through psycho-education, responsive breastfeeding and (c) mother–infant interaction through early stimulation and learning through play (see table 1 for description of intervention sessions).

**Table 1 T1:** Description of intervention sessions

Sessions	Content	Timing	Recipients
1: Introduction and rapport building	Introducing programme and engaging mother and her family Developing empathetic relationship with mother Ensuring family support system	Beginning of 7th month of pregnancy	Mother and family members
2: Maternal well-being	Assessment of psychosocial problems of mother Use of guided discovery and behavioural activation for improving mother’s health (strategies for improving overall well-being, including diet, rest, relaxation and sleep)	7th month of pregnancy	Mother and family members
3: Improving mother relationship with significant others	Thought challenging and behaviour activation using guided discovery (strategies for improving interpersonal relationships and mobilising social support) Awareness about complication during pregnancy	8th month of pregnancy	Mother and family members
4: Improving mother relationship with infant during pregnancy	Thought challenging and behaviour activation using guided discovery (strategies for improving bond with the infant during pregnancy. Knowledge and planning of safe delivery and importance of colostrum)	9th month of pregnancy	Mother
4: Follow-up session after delivery	Following up after child birth Psychoeducation about child development	Immediate postdelivery	Mother

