11: Importance of following child’s interest	Skill-based activities to promote mother–child interaction Homework charts are given to monitor the activity Learning through play activities are reinforced	32 weeks postnatal	Mother and infant
12: Importance of following child’s lead	Skill-based activities to promote mother–child interaction Homework charts are given to monitor the activity Learning through play activities are reinforced	36 weeks postnatal	Mother and infant
13: Promote child language development	Skill-based activities to promote mother–child interaction Homework charts are given to monitor the activity Learning through play activities are reinforced	40 weeks postnatal	Mother and infant
14: Scaffolding	Skill-based activities to promote mother–child interaction Homework charts are given to monitor the activity Learning through play activities are reinforced	44 weeks postnatal	Mother and infant
15: Review of all five strategies	Revision of all strategies and next line of action. Learning through play activities are reinforced.	48 weeks postnatal	Mother and infant

The intervention is designed to be delivered by non-specialist facilitators in 15 monthly sessions in community settings and commences from third trimester of pregnancy and ends at 12 months postpartum. During the COVID-19 pandemic, when the in-person sessions are not possible, we are delivering the scheduled intervention session via telephone. All those sessions delivered via telephone are not repeated in-person.

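### The cost-effectiveness analysis builds its 95% intervals from the 25th and 97.5th bootstrap percentiles, which is a lopsided 72.5% interval; the lower limit should be the 2.5th percentile

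*Protocol article*

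**What the plan says.** The Cost–effectiveness analysis section of the protocol article resamples pairs of costs and effects with replacement, and "bootstrapping sampling will be repeated 1000 times". In each sample, "an estimate of differential total mean costs and expected mean effectiveness will be calculated". The rule for the limits is then: "The 95% CIs for the differential estimates will be derived from the 25th and 97.5th percentiles".

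The same section sets the period for costs: "Primary analysis will be of total costs over the 12 months postpartum follow-up treatment period". It gives the content of the intervention cost without a time limit: "The cost of the intervention will be calculated based on the sum of materials, personnel training and delivery". The Intervention section says that the programme "commences from third trimester of pregnancy and ends at 12 months postpartum".

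**The concern.** The percentile rule states a confidence level and a pair of limits that do not belong together. It stands in the analysis method, not in background text, and nothing elsewhere in the article corrects it.

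An analyst who coded it literally would label as 95% an interval whose lower end is the lower quartile of the bootstrap distribution. Taking differences as intervention minus control (the article does not state the direction), the lower limit would then clear zero far too easily. On the effect side this would overstate the evidence that the intervention improves mother–child interaction. On the cost side it would overstate the evidence that the intervention costs more.

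The effect in the economic analysis is the same outcome as the trial's primary endpoint, for which the Statistical analysis section plans a 95% CI from a linear model. A literal reading could therefore yield two intervals for one difference, both called 95%, that disagree about zero.

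**Working it through.** **Inputs.** From the Cost–effectiveness analysis section: stated level 95%, lower limit 25th percentile, upper limit 97.5th percentile, 1000 resamples. From the Sample size calculations section: 125 per arm and 20% attrition, so 125 × (1 − 0.20) = 100 per arm analysed.

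**1. Level of the interval (no distributional assumption).** Level = upper percentile − lower percentile.
- As written: 97.5 − 25 = 72.5%. The stated 95% is not reproduced.
- With the 2.5th percentile: 97.5 − 2.5 = 95%. Reproduced, with 2.5% in each tail.

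**2. Could 25th be a rank?** With 1000 resamples, the 2.5th percentile is about ordered value 0.025 × 1000 = 25, and the 97.5th is about ordered value 0.975 × 1000 = 975. The 25th ordered value would thus be the right lower limit, but its partner would be the 975th. The text gives 97.5 and calls both limits percentiles. Read literally, the lower limit is about ordered value 0.25 × 1000 = 250.

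**3. Width (assumes an approximately normal bootstrap distribution).**
- The 25th percentile lies at −0.674 SE and the 97.5th at +1.960 SE.
- Width as written: 0.674 + 1.960 = 2.634 SE.
- Width of a 95% interval: 1.960 + 1.960 = 3.920 SE.
- Ratio: 2.634 / 3.920 = 0.67.

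**4. Error when there is no true difference (same assumption).** The lower limit exceeds zero in about 25% of trials instead of 2.5%. The upper limit falls below zero in about 2.5%, as intended. In total the interval excludes zero in about 25 + 2.5 = 27.5% of trials instead of 5%.

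**5. Check with skewed costs.** The plan bootstraps because it expects skewed costs, so steps 3 and 4 were checked by simulation: 2000 trials, 100 per arm, 1000 resamples each, no true difference. Costs were lognormal with log-SD 1, which is an assumption and not a figure from the article.

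| Limits | Coverage | Lower limit above zero |
|---|---|---|
| 25th and 97.5th | 71.45% | 25.4% |
| 2.5th and 97.5th | 94.15% | 2.7% |

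Skewness of this degree leaves the conclusion unchanged.

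**6. Cost period: the texts side by side.** Table 1 places session 1 at "Beginning of 7th month of pregnancy", sessions 2 and 3 in the seventh and eighth months, and the first of two rows numbered 4 in the "9th month of pregnancy". Four sessions therefore precede birth. The sentence on the primary cost analysis names the 12 postpartum months but also calls them a treatment period, and treatment starts in the third trimester. The intervention cost itself has no time limit. Service use is recorded with the Client Services Receipt Inventory at 12 months postpartum only (Table 2 and Maternal secondary outcomes), and the article gives no recall period. These texts do not fix a start date; nor do they exclude the antenatal part.

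**The case against.** The strongest reply is that this is a misprint that corrects itself. Given a 95% level and an upper limit at the 97.5th percentile, the 2.5th is the only lower limit that fits, and a competent analyst would use it. The article also defers detail to a statistical analysis plan that is not at hand. A decimal point lost in reading the PDF cannot be wholly excluded, although the decimal in 97.5 survived in the same sentence. Most of this stands, and it lowers the weight of the point. A reader might infer that the trial will report 72.5% intervals as 95%; the article does not establish that. What it does establish is that the published rule is wrong as worded. That is a misstatement, not a detail left for later.

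A second reply is that the width and SE figures rest on normality, while the plan expects skewed costs. That is correct. Only the 72.5% and the split of the tails follow from the text alone.

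A reader might also infer that the cost analysis starts at birth, drops the four antenatal sessions and so makes the intervention look cheaper than it is. The documents do not support this. Materials, training and delivery are costed without a time limit. Training had to come before any session, so a strict start at birth would remove a component that the plan expressly includes. The phrase can equally be read as naming where the period ends. Four of the 19 rows in Table 1 (4/19 = 21%) are antenatal, but that is a share of contacts, not of cost, and it measures no bias.

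**Conclusion.** The percentile rule is wrong as written: it gives a nominal 72.5% interval, with 25% removed below and 2.5% above, in place of 95%. That part needs no assumption. Under approximate normality, the further consequences are an interval about 67% of the proper width and a lower limit above zero about 25% of the time under no difference. They held in one simulation with assumed lognormal costs.

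The reach is narrow. The primary comparison of mother–child interaction rests on linear models. The incremental cost-effectiveness ratios are point estimates, and the acceptability curves use the resamples directly; none of them depends on these percentile limits. This is a minor but certain correction.

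The cost period is at most an ambiguity between the Cost–effectiveness analysis section and the Intervention section with its Table 1. Neither an omission of antenatal costs nor a bias in favour of the intervention has been shown.

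**What to change.** Change 25th to 2.5th in the sentence on the bootstrap intervals, and carry the same limits into the analysis plan and the code before the economic analysis is run. With 1000 resamples these are about the 25th and 975th ordered values. The cost is one character of text, plus intervals that are wider than the literal rule would give because they have the stated level.

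Separately, reconcile the sentence on the cost period with the third-trimester start of the intervention, saying when the period begins for intervention costs and for service costs in both arms. For intervention costs this is a clarification. For service use, the authors should first check what period the single 12-month interview covers. If it does not reach back into pregnancy, counting antenatal service use would need more than a change of wording, and the article should then state that limit.
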